## Abstract

**Objective:**

To explain the rationale and protocol of the methods and analyses to be used
in the LIVER-PAM randomized clinical trial, which seeks to understand
whether a higher mean arterial pressure is capable of reducing the incidence
of renal dysfunction postoperatively after liver transplantation.

**Methods:**

LIVER-PAM is an open-label, randomized, controlled, singlecenter clinical
trial. Patients randomized to the intervention group will have a mean
arterial pressure of 85 - 90mmHg in the initial 24 hours of postoperative
management, while patients in the control group will have a mean arterial
pressure of 65 - 70mmHg in the same period. A sample of 174 patients will be
required to demonstrate a 20% reduction in the absolute incidence of renal
dysfunction, with a power of 80% and an alpha of 0.05.

**Conclusion:**

If a 20% reduction in the absolute incidence of renal dysfunction in the
postoperative period of liver transplantation is achieved with higher target
mean arterial pressure in the first 24 hours, this would represent an
inexpensive and simple therapy for improving current outcomes in the
management of liver transplant patients.

**ClinicalTrials.gov Registry:**
NCT05068713

## INTRODUCTION

Postoperative patient management after liver transplantation is complex and
challenging, as there is an increased risk to the viability of the graft and to the
survival of the patient.^(1)^ In this
scenario, hemodynamic optimization may be a determining factor in the evolution of
the clinical condition.

Renal dysfunction is one of the most frequent postoperative complications after liver
transplantation and is considered the most important predictor of poor long-term
outcome,^(2)^ as it is
associated with higher mortality^(3)^
and impacts the quality of life, as 18.1% of these patients will have a renal
clearance < 30mL/minute/1.73m^2^ within 5 years.^(4)^ This dysfunction is related to a
combination of preoperative (previous renal function, hepatorenal syndrome and
diuretics), intraoperative (ischemia‒reperfusion injury, shock and bleeding) and
postoperative events (nephrotoxic drugs, water balance and hemodynamic
optimization).^(4)^

One of the classical drivers of renal dysfunction is hypoperfusion, which is closely
linked to mean arterial pressure (MAP).^(5)^ The classic target of MAP > 65mmHg is described as the
safety threshold,^(6,7)^ although a trial employing higher MAP levels showed
lower renal dysfunction in certain subgroups of patients with sepsis.^(8)^ In surgical patients, hypotension
is associated with a higher incidence of acute renal dysfunction, and this risk
increases with the length of the insult.^(9,10)^ A reduction in
other postoperative complications has been observed following hemodynamic
optimization for achieving a MAP closer to the patient’s baseline.^(11)^

In the specific scenario of liver transplantation, retrospective data adjusted for
the propensity score inferred the best renal outcome with a MAP >
90mmHg,^(12)^ while a
physiological evaluation indicated that a reduction in renal blood flow occurs below
a MAP threshold of 75mmHg.^(13)^

Preventing renal dysfunction in the postoperative period may represent an important
way to improve short- and long-term patient outcomes, with blood pressure being a
possible therapeutic target. However, there is no definition of the best blood
pressure target and the exact relationship between different blood pressure levels
and renal outcome. In addition, there are currently few randomized clinical trials
in liver transplant intensive care, during which renal dysfunction is more
frequent.^(12)^ Considering
the current low availability of organs due to the high number of candidate
recipients,^(14)^
understanding tools that may yield better results and reduce complications and
expenses is a priority.

Our hypothesis is that pressure optimization in the first 24 hours after surgery with
higher MAP levels (85 - 90mmHg) is superior to usual care (MAP 65 - 70mmHg) in
preventing acute renal failure in the first 7 days after liver transplantation
surgery.

## METHODS

### Study design

LIVER-PAM will be a single-center, prospective, randomized, open-label,
controlled study in which patients will be randomized to the intervention group
with the highest MAP (85 - 90mmHg) or the control group with the lowest MAP (65
- 70mmHg) for a period of 24 hours after admission to the intensive care unit
(ICU) for liver transplantation. The study will be conducted in the ICU of the
Department of Gastroenterology, Hospital das Clínicas, School of
Medicine, University of São Paulo (USP). The authors reinforce their
commitment to following the guidelines for the reporting of randomized clinical
trials (CONSORT), the international registry of trials and institutional ethical
approval. The study is registered on ClinicalTrials.gov under identification
number NCT05068713, and the study was approved by the Research Ethics Committee
(REC) of the institution under opinion 4,887,829, referring to the second
version of the protocol on September 16, 2022.

### Main objective

The primary goal of the study will be to evaluate whether higher (85 - 90mmHg)
*versus* usual MAP levels (65 - 70mmHg) in the first 24 hours
after liver transplantation are associated with a reduced incidence of acute
renal dysfunction at 7 days, according to the adaptation of the KDIGO
criteria,^(15)^ using a
1.5-fold increase in baseline creatinine as a cutoff point (Appendix 1). Patients who die within the first 7 days
will be considered positive for the main outcome measure.

### Secondary objective

To evaluate whether higher (85 - 90mmHg) *versus* usual MAP levels
(65 - 70mmHg) in the first 24 hours after liver transplantation surgery are
associated with 28-day mortality; retransplantation in 28 days; renal
replacement therapy in 7 days; surgical site infection within 7 days; days alive
and free of renal dysfunction in 7 days; renal dysfunction according to the
values of neutrophil gelatinase-associated lipocalin (NGAL) at admission and
after 48 hours; length of stay in the ICU; length of hospital stay; days alive
and hospitalization-free in 28 days; liver graft dysfunction (initial poor
function subtype) in 7 days; liver graft dysfunction (primary nonfunction) at 10
days and major adverse kidney events at 28 days (MAKE28).

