### Definition of outcomes

The definitions of the outcomes cited above are described in appendix 1 with their respective references.

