antibiotic prophylaxis in the first 24 hours after surgery; use of nephrotoxic
drugs in the first 7 days; immunosuppression in the first 7 days and maximum
tacrolimus level within 7 days; new surgery within 7 days after randomization;
ICU readmission for treatment of complications within 7 days after
randomization; need for retransplantation within 28 days and ICU and hospital
outcome in 28 days (discharge, hospitalization or death).

Data collection will be performed by an external professional (research nurse)
with no connection to the unit. This professional will have access to the data
described but will not have any role in the randomization and management of
patients participating in the study. Such data will be collected in an
electronic form via Redcap® and will remain protected by a
nontransferable password. The professional will perform serial evaluations to
ensure the follow-up of all patients until the 28th postoperative day. The final
result collected will be available, also by means of a password, to the external
professional in charge of the statistical calculations, as well as to the main
researcher.

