### Statistical analysis

The analyses will be performed according to the “intention-to-treat” principle;
all randomized patients will be included in the analysis according to the
treatment group to which they were randomly assigned. Summary statistics per
group, with treatment effects, 95% confidence intervals and p values, will be
presented for the primary and secondary outcomes. Continuous variables will be
tested for normality using the Shapiro‒Wilk test after graphic analysis by
histogram. Parametric continuous variables between two groups will be compared
with the unpaired *t* test and within the same group with the
paired *t* test. If analysis among more than two groups is
required, analysis of variance (ANOVA) will be used. Nonparametric continuous
variables will be evaluated using the Wilcoxon test or the Mann‒Whitney U test
between two groups and the Kruskal‒Wallis test between three or more groups.
Categorical variables will be evaluated using the chi-square test or Fisher’s
exact test, as appropriate. P values < 0.05 will be considered statistically
significant. The outcomes of hospitalization-free days or renal dysfunction over
time will be calculated based on the 7- and 28-day follow-up, respectively,
using Cox regression models. The calculations of survival curves will be
performed with the Kaplan‒Meier method. For the statistical analysis of
outcomes, the results will be adjusted for previous renal function, and logistic
regression will be used to adjust for other confounding factors that generate
inconsistency in the baseline that were not corrected by the randomization of
the study (use of nephrotoxic drugs, maximum tacrolimus level in the first week,
intraoperative fluid balance and intraoperative major bleeding). No statistical
adjustments will be provided for multiple comparisons in the case of secondary
outcomes, and therefore, we suggest that these be interpreted as exploratory
analyses.

The existence of missing data will be described in the publication and managed
with simple exclusion from the analysis. For this study, no interim analyses are
foreseen.

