□ **Acute renal dysfunction according to urinary NGAL assessment**

Number of days during the first 7 postoperative days that the patient was alive
and did not meet the following criteria for renal dysfunction: urinary NGAL
value > 150ng/mL. This outcome will be assessed at admission and at 48
hours.^(2)^

□ **Primary graft dysfunction - initial poor function subtype at 7
days**

Development of one of the following laboratory criteria within the first 7 days
after liver transplantation: bilirubin > 10mg/dL on the seventh day after
transplantation; international normalized ratio > 1.6 on the seventh day
after transplantation; alanine aminotransferase or aspartate aminotransferase
> 2,000IU/L in any of the first 7 days after transplantation.^(3)^

□ **Primary allograft dysfunction - primarily nonfunctional subtype at 10
days (Broering)**

Need for retransplantation in the first 10 days after transplantation or death
due to a nonfunctioning graft.^(3)^

□ **Major adverse kidney events in 28 days (MAKE28)**

The incidence of death, need for renal replacement therapy or persistent renal
dysfunction at 28 days after liver transplantation.^(4)^

□ **Days alive and hospitalization-free in 28 days**

Number of days among the first 28 postoperative days in which the patient was
alive and hospitalization-free.

□ **Major postoperative bleeding at 7 days**

Dichotomous outcome of bleeding that indicates, on the same day, the transfusion
of more than two units of packed red blood cells or the need for surgical
intervention indicated in the first 24 postoperative hours.

□ **Transfusion of blood components in 7 days**

Number of blood components transfused in 7 days separated into packed red blood
cells (one unit equal to one bag), fresh frozen plasma (one unit equal to one
bag), fibrinogen concentrate (one unit equal to 1g) and tranexamic acid (one
unit equal to 1g).

□ **Arrhythmias requiring chemical or electrical therapy within 7
days**

Description in the prescription or medical records of antiarrhythmic or
electrical cardioversion therapy for the first 7 days for treating abnormal
rhythm. A maximum of one event per patient will be considered dichotomously, as
the same event can be reentrant.

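### ICU and hospital length of stay are compared as raw durations with no rule for death, so an arm with more early deaths can appear to have the better stay; ICU stay has no death-aware companion outcome.

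*Protocol article*

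**What the plan says.** The Secondary objective section lists "length of stay in the ICU; length of hospital stay; days alive", where the final words begin a different item: days alive and out of hospital to day 28. Under Definition of outcomes the article states: "The definitions of the outcomes cited above are described in appendix 1 with their respective references". Appendix 1 has no entry for ICU stay or hospital stay. It does define the hospital companion: "Number of days among the first 28 postoperative days in which the patient was" alive and out of hospital.

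The Statistical analysis section gives no method specific to the two stays. Its general rules apply: "Parametric continuous variables between two groups will be compared" by the unpaired t test, and nonparametric continuous "variables will be evaluated using the Wilcoxon test or the Mann‒Whitney U test". Primary and secondary outcomes are to be shown with treatment effects, 95% confidence intervals and p values. Cox models are assigned to the hospitalization-free and renal-dysfunction outcomes, not to length of stay. Missing data are handled "with simple exclusion from the analysis".

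Under Data collection, a research nurse is to "ensure the follow-up of all patients until the 28th postoperative day", and the ICU and hospital "outcome in 28 days (discharge, hospitalization or death") is recorded. The two stay items carry no 28-day limit there.

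**The concern.** A raw duration cannot tell a short stay that ended in discharge from one that ended in death. Compared by a two-sample test, an early death takes one of the most favourable values available. If the pressure target affects early mortality in either direction, the length-of-stay estimate moves the wrong way, and it would still carry a confidence interval and a p value. The trial plans to compare 28-day mortality, so a mortality difference is a possibility it takes seriously.

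The plan deals with death elsewhere. Death within 7 days counts as an event for the primary outcome, and two secondary outcomes count days alive and free of an event. The stays have no such rule. For hospital stay, the companion outcome would show a reader the problem. For ICU stay, nothing would.

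**Working it through.** **Arm size.** The documents give no figure for length of stay, so the only plan figure to reproduce is the total of 174. With 73.7% v 53.7%, two-sided alpha 0.05 (sidedness is not stated, so two-sided is assumed) and 80% power, the unpooled formula gives

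n per arm = (1.960 + 0.842)² × (0.737 × 0.263 + 0.537 × 0.463) / 0.20² = 7.849 × 0.4425 / 0.04 = 86.8, so 87 per arm and 174 in total.

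The figure reproduces. It serves here only to set the arm size.

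**Where an early death ranks.** Assume ICU stay is log-normal with median 6 days and log SD 0.7. The share of undisturbed stays shorter than 2 days is Φ(ln(2/6)/0.7) = Φ(−1.57) = about 6%. A death on day 2 therefore ranks as better than about 94% of stays.

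**ICU stay, simulated.** All inputs are assumptions: the same stay distribution in both arms, deaths spread uniformly over days 1 to 5 and cutting the stay short, 87 per arm, and a two-sided Mann-Whitney test at 0.05. *Favoured* means a significantly shorter raw stay in the arm with more deaths. The last column uses ICU-free days to day 28 with death ranked worst.

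| Deaths | Higher-mortality arm favoured, raw stay | Same arm flagged as worse, death ranked worst |
|---|---|---|
| equal | about 2.5% | about 2.5% |
| 5% v 8% | about 4% | not tabulated |
| 5% v 10% | about 6% | about 8% |
| 5% v 15% | about 11% | about 21% |

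At 5% v 15% the median raw ICU stay is 5.8 v 5.2 days, although the underlying stay distribution is identical. A rerun for this write-up agreed with the table to within about a percentage point.

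**Hospital stay, simulated.** Assume a log-normal stay with median 14 days and log SD 0.6, and exponential time to death with mean 5 days. At 10% v 20% deaths, the mean raw stay is 1.0 to 1.2 days shorter in the higher-mortality arm, which is significantly favoured in about 15% of trials. This holds whether stays beyond day 28 are kept in full, capped or dropped. On days alive and out of hospital, the sign reverses to about 1.1 days against that arm.

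**Stays unfinished at day 28.** The article does not say how these are handled. Assume true medians of 17 v 14 days and 10% mortality in both arms. The mean difference is then 3.2 days with full durations, 2.1 days if capped at 28, and 1.2 days if stays over 28 days are dropped. Dropping dilutes the difference but does not reverse it.

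**The case against.** The strongest reply is that little rests on raw stay. Secondary outcomes are labelled exploratory, 28-day mortality is reported beside them, and hospital stay is paired with a days-alive outcome. The bias is also small unless mortality differs a good deal: 5% v 8% moves the false-favour rate only from 2.5% to about 4%. The largest difference shown would often be visible in mortality itself. At 5% v 15%, the standard error is √((0.05 × 0.95 + 0.15 × 0.85)/87) = 0.045, so power is about Φ(0.10/0.045 − 1.96), roughly 60%. All of this stands, and it keeps the point minor. It does not remove it. The exploratory label is tied to the lack of multiplicity adjustment and does not correct an estimate that can point the wrong way.

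A second reply is that an article may leave such detail to a fuller protocol or analysis plan. That is fair in general. Here, however, the article says its appendix defines the outcomes, the appendix omits these two, and the methods section sets a rule for continuous variables that covers them.

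A third reply is that raw stay answers a fair question about resource use. It does, and it can still be reported descriptively.

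A reader might also infer that stays running past day 28 drop out, because follow-up reaches day 28 and missing data are excluded. The documents do not support that. The stay items have no 28-day limit, still being in hospital is a recorded day-28 status, and nothing classes an unfinished stay as missing. Exclusion is one reading among several; following to discharge or capping at 28 fits the text equally well.

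**Conclusion.** The point holds as a minor one. As written, both stays are plain durations under general two-sample tests with no rule for death, so early death counts as a short stay. The direction of the bias follows from the text. Its size rests on assumed inputs, because the documents give neither stay nor mortality figures. In the ICU scenarios, the wrong arm is significantly favoured in about 4% to 11% of trials against a nominal 2.5%, and the upper end needs mortality to triple. The gap matters most for ICU stay, which has no death-aware counterpart.

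For stays unfinished at day 28, the supportable statement is only that no rule is given. It would go too far to say that such patients are dropped, or that this could make a harmful arm look better: in the scenario checked, exclusion only shrank the difference.

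**What to change.** - **ICU stay:** define it in Appendix 1 and compare it as ICU-free days to day 28, with death by day 28 ranked below every survivor, by a rank test fixed in advance. Alternatively, analyse time to live ICU discharge with death as a competing event and censoring at day 28.
- **Hospital stay:** define it in Appendix 1 and base inference on the days-alive-and-out-of-hospital outcome already listed.
- **Still in the ICU or hospital at day 28:** assign zero free days of the relevant kind and state that these patients are not missing.
- **Raw stays:** report them descriptively only, by survival status.

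The cost is wording. ICU stay, hospital stay and day-28 status are already collected, and the sample size is unaffected. The change should be made before outcomes are analysed, so that the choice cannot depend on the data. One small downside is that free days mix mortality with stay, so deaths and stay among survivors should be shown alongside.

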### Other outcomes (safety)

The safety outcomes to be assessed are the incidence of major postoperative
bleeding at 7 days, transfusion of blood components at 7 days and incidence of
arrhythmias requiring drug or electrical therapy at 7 days.

### Definition of outcomes

The definitions of the outcomes cited above are described in appendix 1 with their respective references.

### Inclusion criteria

All patients older than 18 years of age admitted to the ICU after liver
transplantation will be evaluated for randomization. All patients who receive a
confirmed offer of an organ for liver transplantation and are referred to the
operating room to begin the procedure will be screened for inclusion in the
study. At the end of surgery, patients admitted to the ICU and who are eligible
according to the criteria described here will be randomized within 2 hours of
admission.

### Exclusion criteria

The exclusion criteria were defined with the goals of safety and limiting
confounders, as follows: liver transplantation due to fulminant hepatitis;
liver-kidney transplants; hepatorenal syndrome being treated within 48 hours
pretransplantation; renal replacement therapy in the 15 days prior to
transplantation; persistent refractory shock intraoperatively or on ICU
admission (noradrenaline > 1 mcg/kg/minute associated with a second
vasopressor for more than 2 hours); cardiorespiratory arrest intraoperatively or
on admission; refusal of the physician responsible for the care;
contraindication to the prolonged use of vasopressors; pregnancy; and
retransplantation at an interval of less than 6 months.

Patients or family members will be informed of their right to interrupt the
intervention if they wish to withdraw from participation at any stage of the
study. The team of professionals involved in the care of these patients will be
informed of their rights to interrupt the protocol according to clinical
judgment or in the event of a serious adverse event attributed to the
intervention.

### Randomization and blinding

Patients will be randomized within 2 hours of ICU admission after liver
transplantation using a simple 1:1 allocation sequence without group
stratification. The randomization will be performed electronically by the
randomization tool of the Redcap® system. The randomization sequence will
be generated *online* and entered into the system by a staff
member who will not participate in the participant tracking process, in
obtaining informed consent from the patient or in the clinical management of the
cases. The researcher will also not participate in the evaluation of the study
outcome data in order to ensure compliance with the allocation concealment
process.

As the interventions in both groups are based on target MAP levels to be followed
by the professionals involved in the care, the authors chose not to blind the
interventions, which, although possible, would be complex to perform in the
center in question. However, the professional responsible for collecting the
outcome data will be an external research nurse, with no affiliation with the
institution where the study is conducted and who is not involved with the care
offered to each patient. The same care will be taken to hire the statistician
who will analyze the results, ensuring that he or she will not be aware of the
allocated groups. To minimize the risk of bias, an objective primary outcome was
chosen based on test results measured by a certified laboratory.

### Intervention

#### General management (both groups)

All patients will be treated according to the current care protocol of the
institution, which aims to achieve normal oxygenation (oxygen saturation -
SpO2 ≥ 94%), hemoglobin (≥ 7g/dL), body temperature (≥
35ºC) and cardiac index (> 2.5L/minute/m^2^) levels.
Professionals on duty not participating in the study will determine fluid
infusion based on clinical criteria including heart rate, cardiac index,
blood pressure, urine output, core-peripheral temperature gradient, serum
lactate level and base excess. The MAP will be determined according to the
allocated group until 24 hours after admission to the ICU have passed. The
use of antibiotic prophylaxis will be defined by the team of transplant
infectiologists before patient randomization; the initial and subsequent
immunosuppressive doses will be defined by the surgical team according to
the institutional protocol. The hemodynamic variables will be monitored by
means of an invasive pressure catheter, pulmonary artery catheter and/or
ultrasonography. Our priority is to construct a pragmatic protocol that
could increase adherence to the trial. Given that the study setting is a
public ICU in a low/middle income country with limited human
resources,^(16)^ the
heterogeneity of the actors involved and the widespread number of admissions
for transplants, the indications for fluids, the type of fluid and the rate
to be infused will be left to the discretion of the attending physician;
these data will be collected and described in the results. The discretion of
the attending physician also extends to the use of inotropes because
although the institutional practice is to use such inotropes only when the
cardiac index is below the reference value mentioned above, this practice
requires individualization in cases of portopulmonary hypertension, in that
the use of milrinone may be requested individually.

